#### Intervention

The clinical psychiatric nurses will run the intervention. They will be trained face-to-face for 2 days by the research team and will be required to master the contents and methods of the WeChat-based self-compassion intervention. Clinical psychiatric nurses who pass the examination will act as the nurses responsible for the WeChat-based self-compassion training intervention. The training protocol developed by the researcher is totally independent and different from the clinical education received at the hospital. The “Self-compassion Tour” module includes the following three tasks: a reading task, a meditation task, and a self-compassion journal task. Each message in the intervention will be compiled by one research team member who will develop appropriate multimedia content using videos, pictures, or records to effectively convey the meaning of each message. Each message will be revised according to expert opinion and subsequently approved by the research team members. The messages will be published on the WeChat public account “Self-compassion Tour” every day on time. Each task is described in detail below. The key themes of the “Self-compassion Tour” are summarized in Table 1. The function of the “Self-compassion Tour” system is shown in Figure 2. The interface of the “Self-compassion Tour” is shown in Figure 3.

**TABLE 1 T1:** Key themes of the “Self-compassion Tour”.

Week	Theme	Task		
		
		Reading task	Meditation task	Self-compassion journal task
Week 1	Understanding self-compassion	Introduction of self-compassion	The compassionate body scan	Keep a journal from perspectives of mindfulness, a sense of common humanity and kindness
Week 2	Understanding self-criticism and stigma	Stories of being self-kindness to oneself who are also suffering from schizophrenia	loving-kindness meditation	Keep a journal from perspectives of finding your own strengths
Week 3	Improve treatment adherence	Stories of Coping with difficult feelings and emotions of adhering to treatment	Affectionate Breathing	Keep a journal from perspectives of encouraging yourself to recovery

**FIGURE 2 F2:**
[figure not shown]
Function of the ‘Self-compassion Tour’ system. Figure created with Microsoft Office PowerPoint.

**FIGURE 3 F3:**
[figure not shown]
The interface of the ‘Self-compassion Tour’. **(A)** Notification of new messages, **(B)** reading task, **(C)** meditation task, **(D)** self-compassion journal task. Figure created with Microsoft Office PowerPoint.

##### Reading task

The content provided for reading will be updated daily according to the theme of the week. Participants will be able to read the new messages and review the message history of all content published on the WeChat public account. The messages will be shown in the form of text, videos, and pictures. The content of the first week will be focused on theoretical knowledge in relation to self-compassion. The aim is for participants to understand the meaning of the three levels of self-compassion and be able to start the self-compassion journal task. The second and third weeks will be focused on positive stories about people suffering from schizophrenia. These 2 weeks are a complement to the “sense of common humanity” gained in group therapy, where patients are able to view their experiences as part of a common experience of many people with schizophrenia (Lawrence and Lee, 2014), fostering acceptance by other group members (Ashfield et al., 2020). Reading new messages on the WeChat group will take approximately 10 min every day. At the end of the reading, two small tests will be inserted to check whether the participant has read the content carefully.

##### Meditation task

In the 3-week online self-compassion meditation intervention, participants will be asked to listen to an audio recording regularly each week (at least once per day) (Albertson et al., 2015). Three different guided self-compassion meditations that were taught in the MSC program will be used for the intervention (Neff and Germer, 2013). For example, the first week will be the “compassionate body scan,” which aims to help the participant feel connected with their body and give their body sympathy, peace, and gratitude. Accompanied by the audio, the participants will be asked to sit or lie down, put their hands on their heart, remind themselves to be kind to themselves, and then scan from the top of their head to their feet and pay attention to the feeling of every part of the body. The task will take approximately 10 min every day.

##### Self-compassion journal task

This task is a modification of the self-compassion journal exercise on [name] self-compassion website.^1^ The content of the weekly journal will differ in relation to the theme of the week. For example, in the first week, participants will be asked to “keep a journal from the perspective of mindfulness, a sense of common humanity and kindness.” They will be presented with prompts, such as “at some point during the day when you have a few quiet moments, write in your journal about anything that you felt bad about, anything you judged yourself for, or any difficult experience that caused you pain. For each event, use mindfulness, a sense of common humanity, and kindness to process the event in a more self-compassionate way.” Participants will be asked to try to write in their daily self-compassion journal for approximately 15 min, with guidance. All diaries will be delivered to the clinical psychiatric nurses via online documentation links on the WeChat public account, and participants will be instructed on the basis of their writing in order to better use the three components of self-compassion to help them actively cope with difficult emotions.

Task completion will be tracked every day. When the participant completes the task for the day, they will be required to click “I have completed the task” in the WeChat group; if the participant fails to complete the task before 8.00 p.m. that day, they will receive a private WeChat reminder message from the clinical psychiatric nurse. If participants have any questions about task completion, they will be able to leave a message on the WeChat public account, and the clinical psychiatric nurse will reply as soon as possible. All questions and answers on the WeChat public account will be visible to all participants in the intervention group (all the participants will be assured of anonymity by using special code numbers to identify themselves). The information forwarding function will be disabled, and participants will be told not to share the messages with others, such as by taking screenshots, in order to minimize potential contamination.

The control group will follow another WeChat public account which will provide psychological health education. Participants in the control group will only be required to read excerpts of articles from books about psychological health. The articles will be organized into three sections (one section per week): challenges faced by those with mental disorders, signs of bad emotions, and psychological health self-management recommendations. The articles will be updated daily for 3 consecutive weeks.

Adverse events, if any, are expected to be minor. At the start of every week, participants will be asked whether they experienced any physical discomfort, emotional discomfort or distress, or an increase in problems in relationships with others in the past week. With regard to reporting adverse events, data from the intervention and control arms will be combined, and descriptive statistics will be used to evaluate the frequency and severity of adverse events. All collected adverse events will be reported.

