### Design

#### Trial design

The study will be an exploratory, parallel randomized controlled trial (RCT) comparing a 3-week WeChat-based self-compassion training protocol to a control condition with only WeChat-based psychological health education. The effects of the intervention on treatment adherence, self-compassion, stigma, and social support will be evaluated among patients with schizophrenia. Eligible participants will be randomly allocated to one of the two conditions (intervention or control) at a ratio of 1:1. The Consolidated Standards of Reporting Trials (CONSORT) (Schulz et al., 2010) flowchart is presented in Figure 1. The study protocol was developed and reported according to the Standard Protocol Items: Recommendations for Interventional Trials (SPIRIT) 2013 statement (Chan et al., 2013; Supplementary File 1).

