**Abscission criteria:**

(1)Patients have deteriorated mental conditions during the course of the study.(2)Patients quit the study.(3)Patients could not be contacted during the intervention, and they did not complete the intervention tasks as required.(4)Patients did not complete post-intervention evaluation.

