#### Sample size

The sample size of the study was calculated using the G*Power 3.1 software package (Faul et al., 2007). With a power of 0.80, an alpha set at 0.05, and an effect size of 0.3 for the primary outcome, the Medication Adherence Rating Scale (MARS) score (Çetin and Aylaz, 2018), it was determined that each group would need 176 patients with schizophrenia. Given an attrition rate of 10%, a minimum of 392 participants (196 in each group) is required.

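### Adverse events are to be reported with both arms combined, so the planned report cannot show whether the training causes excess events

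*Protocol article*

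**What the plan says.** The adverse-event plan is in the last paragraph on the intervention, after the control condition (under the heading Self-compassion journal task).

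- Expectation: "Adverse events, if any, are expected to be minor".
- Ascertainment: "At the start of every week, participants will be asked whether they experienced any physical discomfort, emotional discomfort or distress", followed by an item on worsening relationships. The question is put to participants generally, with no restriction to one arm.
- Reporting: "data from the intervention and control arms will be combined, and descriptive statistics will be used to evaluate the frequency and severity" of adverse events.
- Completeness: "All collected adverse events will be reported". This does not say by arm.

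Participants are "randomly allocated to one of the two conditions (intervention or control) at a ratio of 1:1" (Trial design). Statistical methods names between-group models for adherence, self-compassion, stigma and social support, and descriptive statistics for feasibility and acceptability. It does not mention adverse events. The Abscission criteria list, as the first reason for drop-out, "Patients have deteriorated mental conditions during the course of the study". No section says that such a case counts as an adverse event.

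**The concern.** The pooling is stated outright. It is therefore not a detail left to a full protocol or analysis plan, and an analysis plan that followed the sentence would carry it forward.

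The two programmes ask different things of participants. The intervention arm reads, meditates and keeps a journal every day, and the week 1 journal prompt asks about painful experiences. The control arm only reads articles. Whether the training adds distress is a natural question in people with schizophrenia, and randomisation gives a fair comparison to answer it. A combined figure sets that comparison aside.

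The answer matters after the trial. If the programme is effective, the Conclusion foresees its use in hospitals and communities, and Ethical considerations promises it to the control group. Both steps call for a view on harm as well as benefit.

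Deterioration of mental condition raises a related, smaller issue. It is handled as a reason for drop-out, and nothing places it beside the adverse events.

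**Working it through.** **The plan's own figure.** The adverse-event paragraph states no number. The arm size comes from Sample size: "With a power of 0.80, an alpha set at 0.05, and an effect size of 0.3 for the primary outcome". A two-sided two-sample t-test with these inputs needs 175.4, so 176 per group. Allowing for 10% attrition, 176 / 0.90 = 195.6, so 196 per group and 392 in total. This agrees with the plan and is not in question.

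**What a pooled rate contains.** Let x_I and x_C be the numbers of participants with at least one event, and n the size of each arm.

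pooled rate = (x_I + x_C) / 2n = (p_I + p_C) / 2

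The difference p_I - p_C does not appear in it. For example, a pooled 26/392 = 6.6% is compatible with any difference from -26/196 = -13.3 points to +26/196 = +13.3 points.

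**By arm, with assumed counts.** The document gives no event rates, so these splits are assumptions. All have the same pooled 26/392. The interval is d ± 1.96 × √[p_I(1 - p_I)/196 + p_C(1 - p_C)/196].

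| Split (intervention v control) | Rates | Difference | 95% CI | Fisher p |
|---|---|---|---|---|
| 20 v 6 | 10.2% v 3.1% | 7.1 points | 2.3 to 12.0 | 0.007 |
| 16 v 10 | 8.2% v 5.1% | 3.1 points | -1.9 to 8.0 | 0.31 |

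For 20 v 6: SE = √(0.1020 × 0.8980/196 + 0.0306 × 0.9694/196) = 0.0249, and 7.1 ± 1.96 × 2.49 gives 2.3 to 12.0.

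For 16 v 10: SE = √(0.0816 × 0.9184/196 + 0.0510 × 0.9490/196) = 0.0251, and 3.1 ± 1.96 × 2.51 gives -1.9 to 8.0.

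The planned report would show 6.6% in both cases.

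**A higher assumed rate.** A pooled 15% arises from each of these (intervention v control):

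- 15% v 15%: difference 0 (95% CI -7.1 to 7.1)
- 20% v 10%: difference 10 points (3.0 to 17.0)
- 25% v 5%: difference 20 points (13.2 to 26.8)

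**What by-arm reporting can detect.** With 196 per arm and a two-sided 5% level, power is about 91% for 15% v 5%, 79% for 20% v 10%, and 47% for 10% v 5%. Small differences would be estimated with wide intervals and often not separated from zero.

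**The case against.** Several points can be made for the plan.

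- **The trial can still show harm.** A reader might infer from the pooling sentence that the trial itself cannot detect harm. That goes too far. Allocation is known for every participant and the weekly question is not restricted to one arm, so the data could be split at any time before tables are made. Only the planned report is deficient.
- **Deterioration does not necessarily vanish.** A reader might also infer that patients who deteriorate leave the safety table altogether. The document does not say so. The weekly question on emotional discomfort or distress and on relationships may capture some of them, and all collected events are to be reported. What stands is narrower: no section labels deterioration an adverse event.
- **The control material is not clearly free of distress.** It covers the challenges of mental disorder and signs of bad emotions, and the journal themes in weeks 2 and 3 are strengths and encouragement. The direction of any difference should therefore not be presumed, which is itself a reason to show both arms.
- **Safety is not an aim.** The trial is described as exploratory, events are expected to be minor, and the adherence result is untouched. This limits the weight of the point but gives no reason to combine the arms.
- **Blinding.** Combining arms would be reasonable for blinded monitoring during the trial. The sentence concerns reporting and gives no such reason. Blinded analysts can tabulate under masked arm codes, as they must for the efficacy models.

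**Conclusion.** The point holds for the planned report. Followed as written, it yields one combined figure from which no effect of the training on adverse events can be read, at any event rate. This conclusion rests on the pooling sentence and on equal arms; with slightly unequal arms the pooled rate becomes a weighted average, and the conclusion is the same.

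The size in points rests on assumed counts. The same 6.6% can hide a difference of 7.1 points that excludes zero or one of 3.1 points that does not. Neither split is a forecast. Reporting by arm will not guarantee a clear answer, since power is about 47% for 10% v 5%, but it gives an estimate with its uncertainty where the present plan gives none.

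**What to change.** Replace the pooling sentence with descriptive reporting by randomised arm: the number and percentage of participants with at least one adverse event, by type and severity, with the risk difference and 95% CI. State that the differences are to be read as estimates, because power for small differences is limited. A combined column may be kept beside the two arms.

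Add a row, by arm, for drop-outs due to deteriorated mental condition, placed with the adverse events. Note that the weekly distress question may already count some of these patients, so the two rows can overlap.

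Cost: one sentence and a table with a column for each arm, and no added patients. For the weekly items no new data are needed. The deterioration row needs the reason for each drop-out to be recorded in the same way in both arms. The article does not say how or by whom deterioration is judged, so that takes a little more work.

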#### Statistical methods

The baseline characteristics of the sample will be compared using χ^2^-tests for categorical variables and Student’s *t*-test or Mann–Whitney *U*-test for quantitative variables.

Statistical analyses will be performed on the basis of the intention-to-treat approach, which will include all randomized participants. The extent of missing data will be analyzed. We will explore missing data patterns and determine the type of missing data (missing completely at random, missing at random, and not missing at random). We will use multiple imputations to substitute missing values and conduct sensitivity analyses for datasets with and without imputed data.

Descriptive statistics will be used to evaluate study feasibility and acceptability. We will use linear mixed models with time (pre-intervention vs. post-intervention measures) as a within-group effect, study condition (intervention condition vs. control condition) as a between-group effect, and the interaction effect between these two effects to evaluate the efficacy of the WeChat-based self-compassion training intervention on patient adherence, self-compassion, stigma, and social support. This primary analysis will be performed using the data from the baseline and 3-week post-assessment. We will conduct within-group analyses using repeated measures ANOVA (pre-intervention, post-intervention, and follow-up measures) and paired *t*-tests when comparing only two time points to analyze the stability of the short-term effects of the intervention on patient adherence, self-compassion, stigma, and social support. Moreover, the correlation among self-compassion, stigma, social support, and patient adherence will be analyzed using Pearson correlation. The results will be reported with 95% confidence intervals. Bilateral *p* ≤ 0.05 shows a statistically significant difference. All data will be analyzed using SPSS 24.0.

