### Ethical considerations

This study was approved by the Human Research Ethics Committee (REDACTED). All participants and one of their family members will be required to sign an informed consent form, which includes details of the intervention goals and procedures. Interventions and questionnaires will be conducted after written informed consent is obtained from each recruited participant. Participants will be informed of the freedom to withdraw from the study at any time and will be assured of anonymity by using special code numbers to identify themselves. All of the collected data will be pseudo-anonymized and kept confidential. Only members of the research team will be able to re-identify the participants. If the intervention proves to be effective, then participants in the control group will also receive the WeChat-based self-compassion training after the study is completed. The trial is registered at the Chinese Clinical Trials.gov.

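### Adverse events are to be summarised with the two arms combined, so the planned summary cannot show whether the training causes more discomfort or distress than the control reading

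*Protocol article*

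**What the plan says.** The adverse-event plan stands at the end of the Intervention section, after the description of the control condition. Collection is systematic and is not restricted to one arm: "At the start of every week, participants will be asked whether they experienced any physical discomfort, emotional discomfort or distress", and relationship problems are asked about as well. For reporting, "data from the intervention and control arms will be combined, and descriptive statistics will be used to evaluate the frequency and severity" of the events. The next sentence undertakes to report every event that is collected. It does not say by arm.

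The Statistical methods section specifies between-arm linear mixed models "to evaluate the efficacy of the WeChat-based self-compassion training intervention on patient adherence, self-compassion, stigma, and social support". Adverse events are not in that list.

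Three other places bear on the point:

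- The arms differ in what they do each day. Training participants meditate ("The task will take approximately 10 min every day") and write a journal for roughly 15 minutes; controls read articles. The week 1 journal prompt is to "write in your journal about anything that you felt bad about, anything you judged yourself for, or any difficult experience that caused you pain".
- The Abscission criteria include "Patients have deteriorated mental conditions during the course of the study".
- Under Ethical considerations, "If the intervention proves to be effective, then participants in the control group will also receive the WeChat-based self-compassion training" once the study is over.

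**The concern.** A randomised control arm allows events caused by the training to be told apart from events that would have occurred anyway. In recently recovered patients with schizophrenia some discomfort and distress is to be expected in both arms, so a single overall frequency is hard to interpret. The trial collects what is needed for a randomised comparison and then states that it will merge the arms.

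This is not a detail left to an unseen analysis plan, because the article itself prescribes the pooling. What is at stake is the safety statement that accompanies the efficacy result. If the training is judged effective, controls are to be offered it, and the Conclusion foresees use in hospitals and communities. A reader of the planned summary could not say whether the training arm reported more distress than the reading arm.

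**Working it through.** **Inputs from the article.** Allocation 1:1 (Trial design). 176 per group before and 196 per group after 10% attrition, 392 in total (Sample size). These figures reproduce: a two-sample t-test with effect size 0.3, two-sided alpha 0.05 and power 0.80 needs 175.4, rounded up to 176; 176 / 0.9 = 195.6, rounded up to 196. They are not in dispute and serve only as denominators.

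**Inputs assumed.** The article gives no adverse-event rate. Every count below is an assumption, chosen to show what pooling hides, and counts participants with at least one event.

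**Step 1: what a pooled rate says about the difference.** With equal arms p = (pT + pC)/2, so pT + pC = 2p. Neither rate can be negative, so for p up to 50% the difference d = pT − pC can lie anywhere from −2p to +2p.

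| Participants with an event, of 392 | Pooled p | Range left open for d |
|---|---|---|
| 20 | 5.1% | −10.2 to +10.2 points |
| 40 | 10.2% | −20.4 to +20.4 points |
| 80 | 20.4% | −40.8 to +40.8 points |

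The pooled figure caps the size of a difference, and more tightly when events are rare. It gives neither a sign nor an estimate.

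**Step 2: same pooled report, different trials.** Take 40 of 392. The pooled report is 10.2% (Wilson 95% CI 7.6 to 13.6) in every row. The by-arm interval is Newcombe's: lower = d − √[(pT − lT)² + (uC − pC)²], upper = d + √[(uT − pT)² + (pC − lC)²], where l and u are Wilson limits with n = 196.

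| Training v control | d (points) | 95% CI |
|---|---|---|
| 20 v 20 | 0.0 | −6.1 to 6.1 |
| 25 v 15 | 5.1 | −1.0 to 11.3 |
| 30 v 10 | 10.2 | 4.3 to 16.4 |

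Last row in full: pT = 30/196 = 15.31% (Wilson 10.94 to 21.01); pC = 10/196 = 5.10% (2.79 to 9.14). Lower = 10.20 − √(4.37² + 4.04²) = 10.20 − 5.95, about 4.3. Upper = 10.20 + √(5.70² + 2.31²) = 10.20 + 6.15, about 16.4. A threefold rate in the training arm and no difference at all would give the same planned summary.

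**Step 3: what a by-arm table could show.** Wald half-width with the same rate p in each arm: 1.96 × √[2p(1 − p)/n].

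| Assumed rate per arm | n = 196 | n = 176 |
|---|---|---|
| 5% | 4.3 points | 4.6 points |
| 10% | 5.9 points | 6.3 points |
| 20% | 7.9 points | 8.4 points |

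For 10% and n = 196: 1.96 × √(0.18/196) = 1.96 × 0.0303 = 0.059.

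The smallest training count whose Newcombe interval lies above 0, with 196 per arm, is 21 against 10 controls (5.6 points, 0.2 to 11.2), 34 against 20 (7.1, 0.3 to 14.0) or 56 against 39 (8.7, 0.2 to 17.0). Only fairly large excesses would stand out.

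**The case against.** The strongest reply is that little is lost. The trial is described as exploratory and events are expected to be minor. The article promises to report every collected event, and the data stay separable by arm. Worsening is not wholly invisible either: self-compassion and stigma are compared between arms, nurses read and respond to the journals, and withdrawals for deterioration may appear by arm in the flowchart. Even a by-arm table would reveal only large excesses.

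Much of this stands, and it limits the weight of the point. It does not remove it. Complete reporting is not reporting by arm, and the pooling sentence immediately before it states how the events will be summarised. Separable data make the repair cheap, but the written plan is not to separate them. Self-compassion and stigma scores are indirect signals and do not stand in for the weekly answers on discomfort and distress. Limited precision is a reason to show an interval.

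A reader might go further and infer three things that the article does not support:

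- **That a pooled rate says nothing about the difference.** It does bound it, as Step 1 shows.
- **That the training is likely to distress patients.** No event rate is given. The prompt about painful events is documented for week 1; the week 2 theme is "Keep a journal from perspectives of finding your own strengths", week 3 turns to encouragement, and nurses give guidance on the entries.
- **That the offer of training to controls needs a new safety condition or disclosure.** The defect lies in a reporting sentence, and correcting that sentence is enough.

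**Conclusion.** The point holds as a reporting defect fixed in the text. Followed as written, the adverse-event summary gives up the randomised comparison of harms and cannot show whether the training arm had more discomfort or distress than the reading arm. With an assumed 40 of 392 participants affected, it leaves open any difference within plus or minus 20.4 points.

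The size rests on assumed counts and on 196 participants per arm answering; with 176 the by-arm intervals are slightly wider. That pooling gives no sign and no estimate rests only on the equal allocation. The efficacy analysis is unaffected. The change should be made because it is cheap and recovers a comparison that the trial has already paid for.

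**What to change.** Replace the pooling sentence in the Intervention section with wording to this effect:

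> Adverse events will be tabulated by arm under coded labels: number of participants answering; number and percentage with at least one event of each type occurring after the start of the intervention; severity; and number of withdrawals for deteriorated mental condition. Between-arm differences will be given with 95% confidence intervals. The table is descriptive, with no significance test. A pooled total may be added.

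The cut-off should be the start of the intervention and not randomisation. A question put at the start of week 1 about the past week would be answered after allocation but would cover time before any training or reading.

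The cost is one sentence and one extra table from data already collected weekly. Coded labels keep the analysts blinded, since the planned mixed models already need an arm code. The downside is limited precision, about 6 points either side at an assumed 10% per arm with 196 per arm, so the report should say that the absence of a clear difference is not evidence of no excess. No change is needed to the Ethical considerations section or to what controls are told.
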